#### 2.8.3. Rehabilitation of Sensorimotor Functions—Exercise Tolerance Functions

Exercise tolerance functions, including physical endurance, aerobic capacity, and reliability, will be treated with the following:General physical endurance exercises;Gradual, progressive, and prolonged aerobic exercises;Fatigue control and management at varying effort levels.

Objectives of these exercises will be (i) improvement of endurance and (ii) reconditioning of cardiovascular and respiratory systems.

#### 2.8.4. Rehabilitation of Specific Mental Functions

Specific mental functions (attention, memory, perceptual functions, higher-level cognitive functions, language and calculation mental functions, and self- and time-experience functions) will be treated with the following:Attention training exercises (e.g., visual search exercises, barrage);Memory training exercises (e.g., repetition and delayed recall of word lists);Recognition and interpretation exercises of sensory stimuli;Exercises for higher-level cognitive functions (e.g., decision-making processes, planning, problem-solving, etc.);Exercises for language-specific mental functions (recognition and use of signs, symbols, and other language components);Exercises for specific mental functions of simple mathematical calculations and complex mathematical operations;Exercises for awareness of one’s identity in the reality of one’s environment and time.

Objectives of these exercises will be (i) improvement in patient orientation in spatial–temporal dimensions and patient’s reality orientation; (ii) increase in short-term memory spans; (iii) improvement in attention times and concentration capacity on a task; (iv) improvement in selective and sustained attention; (v) improvement in language comprehension and production skills; and (vi) maintenance of acquired and residual skills in daily life.

#### 2.8.5. Rehabilitation of Activities and Participation, Self-Care, and Daily Life Activities

Daily life activities (washing, grooming, dressing, eating, etc.) and participation will be treated with the following:Exercises of learning and application of learned knowledge and problem-solving;Execution of single or multiple tasks and routine organisation exercises;Mobility (postural passages; transfers; object transportation and movement; task-oriented and manipulation exercises; walking and moving in different places and using devices);Activities aimed at self-care, washing and drying, dressing, and eating;Performance of domestic and daily activities;Reintegration into social life.

Objectives of these exercises will be (i) improvement of executive functions (problem-solving) with compensation strategies; (ii) safety protection (risk of falling); (iii) improvement of movement control and precision; (iv) identification and elimination of environmental barriers; (v) improvement of physical, psychological, and social adaptation capabilities; and (vi) identification of strategies aimed at carrying out daily life activities (personal care, work, school, and leisure time).

### 2.9. Specific Interventions

#### 2.9.1. Experimental Group: Integrated Treatment with Robotic and Technological Devices

The experimental intervention involves administering a rehabilitative treatment, as described above, using (also) RADTs. Based on the equipment available at each centre, different devices may be used; however, harmonisation of the treatments provided across all centres will be ensured by using, in each centre, devices that enable rehabilitation in the following domains:(A)Upper limb sensorimotor abilities;(B)Lower limb sensorimotor abilities and gait;(C)Balance;(D)Cognitive abilities.

To ensure a standardised treatment for patients enrolled in the different centres and randomised into the experimental group, a precise and punctual rotation of the four domains listed above has been adopted. The treatment plan dictates that, starting from the first day, patients will address domain A, followed by domain B on the second day, and so on, continuing with the A-B-C-D sequence until the completion of 25 total treatment sessions, as illustrated in Figure 2. This strict rotation ensures a consistent and balanced delivery of the intervention, always following the domain sequence to guarantee a standardised rehabilitation.

Specifically, for rehabilitating sensorimotor function of the upper limb (Domain A) in the proximal (shoulder), semi-distal (elbow), and distal (hand) regions, the following devices may be used:Planar end-effector robots for shoulder-elbow rehabilitation, or exoskeletons or electromechanical systems for shoulder, elbow, and wrist rehabilitation;End-effector robots or exoskeletons for the hand;Sensor-based devices for comprehensive upper limb treatment.

For rehabilitating sensorimotor function of the lower limb (Domain B), the following ones will be considered:End-effector robots or exoskeletons (overground and non-overground) for the lower limb;Treadmills with body-weight support systems.

Balance training under static and dynamic conditions (Domain C) will be ensured by the following:
Robotic and digital stabilometric platforms;Sensor-based systems.

For cognitive functions (Domain D), digital systems, sensor-based devices, and virtual reality programmes will be used to train memory, attention, visuospatial skills, and executive functions.

The treatment will be conducted within a gym equipped with devices enabling treatment of all identified domains, following a predetermined rotation, as previously illustrated, where two physiotherapists will supervise a group of patients ranging from 4 to 6, depending on the severity of their clinical condition. In each robotic session, at least 100 repetitions are performed. All devices used in the study must already have a CE mark for medical devices and be used according to the manufacturer’s intended use.

Information on the experimental intervention with RADTs was reported following the Template for Intervention Description and Replication (TIDieR) Checklist [55].

#### 2.9.2. Control Group: Traditional Treatment

In the control group, subjects will undergo a standard traditional rehabilitation programme without the use of RADTs, focusing on activities and objectives mentioned in the section “Interventions”, using traditional methods of physiotherapy and cognitive rehabilitation. As in usual clinical practice, a physiotherapist-to-patient ratio of 1:1 is provided for the treatment in all participating centres.

### 2.10. Intervention Schedule

Patients in the experimental/control group will undergo a total of 25 robot-assisted/traditional sessions, each lasting 45 min, with the following frequency:Five times a week for 5 weeks, for inpatients;Three times a week for 8.3 weeks, for outpatients.

The difference in treatment frequency between the two settings is related to current regulations and the difficulty as an outpatient to travel to urban rehabilitation facilities on a daily basis. This approach ensures that patients receive the same number of rehabilitation sessions and are able to attend all scheduled sessions, thus reducing the risk of potential dropouts.

In addition, according to current Italian regulations, which require providing inpatients with 3 sessions/day of treatment for 6 days/week, all inpatients (also those randomised in the intervention arm) will undergo, in addition to the 25 sessions, traditional rehabilitation sessions (neuromotor and occupational therapy, according to patient’s need) (6 times/week), lasting 45 min. To avoid the possibility of performance bias, the therapists who will treat subjects in RADT-assisted treatment will be different from therapists who will treat the same subjects traditionally. Moreover, according to the medical prescription, all subjects (inpatients and outpatients) will undergo one session/day of cognitive, occupational, speech, or swallowing therapy based on their needs. The intervention provided to patients in both groups, in inpatient and outpatient settings, is reported in Figure 3.

All rehabilitation sessions, including type (neuromotor, occupational, cognitive, occupational, speech, swallowing therapy), method (robotic or conventional), duration in minutes, and possible issues arising, will be recorded daily by the therapists (session diary).

### 2.11. Intervention Adherence

High adherence to the study is expected, as patients will undergo treatment during the period of admission to the rehabilitation facilities (albeit in different settings, inpatient or outpatient, depending on the severity of the clinical condition) in accordance with current regulations. To ensure the quality and consistency of the intervention, adherence will be carefully assessed by an independent team of clinical operators, who will regularly monitor the session diary. If needed, targeted strategies will be implemented to maintain and improve adherence, including periodic training sessions for the involved staff and providing timely feedback to the therapists involved in treatment in both study groups.

### 2.12. Outcome Assessments

#### 2.12.1. Primary Endpoint

The primary endpoint of the study will be the change in the modified Barthel Index [35] between the beginning and the end of the treatment (T1–T0).

#### 2.12.2. Secondary Endpoint

The study includes numerous secondary outcomes aimed at capturing changes in patients who may have very different sensorimotor functions and performances, considering that we are examining patients within the first 6 months after the acute event and in different settings.

1.Treatment effects, measured by clinical scales at the beginning (T0) and end of the treatment (T1)
Fugl–Meyer Assessment for the upper extremities (upper limb sensorimotor domain) [29];Fugl–Meyer Assessment for the lower extremities (lower limb sensorimotor domain) [29];Berg Balance Scale (balance domain) [31];Symbol Digit Modalities Test (cognitive domain) [56].

Additional scales in accordance with the domains of the ICF:
Body function
aModified Ashworth Scale [33];bMotricity Index (upper and lower extremities) [57];cTrunk Control Test (TCT);dNumerical Rating Scale for Pain [58];eDouleur Neuropathique 4 [59];fActivities;gAction Research Arm test [60];hTwo-Minute Walk Test [61].

Participation
a.EQ-5D-5L [62].
2.Treatment Effects—Neurophysiology

At the beginning (T0) and end of the treatment (T1), all patients will undergo a neurophysiological evaluation through high-density resting electroencephalography (EEG) to study the neurophysiological recovery processes. Both groups of patients will undergo high-density EEG recording using a 64-channel HD-EEG system. The signals will be acquired using a cap with 64 electrodes positioned according to the international 10/20 montage. Contact impedance will be maintained below 5 KΩ. Recordings will be made for 10 min with eyes open and 10 min with eyes closed, with the subject relaxed and in a comfortable supine position. Specifically, from the recorded signals, the Brain Symmetry Index (BSI) [63,64], a quantitative electroencephalographic (qEEG) measure used to assess the degree of symmetry in brain activity between the two hemispheres, and the Delta/Alpha Ratio (DAR) [65], a qEEG measure used to assess the balance between slow-wave (delta) and fast-wave (alpha) brain activity, will be obtained.

3.Treatment Effects—Biochemical Analysis

In all patients, changes in the levels of BDNF, neurofilament light (NfL), and glial fibrillary acidic protein (GFAP), which are factors involved in neuroplasticity and tissue damage, will be evaluated. Specifically, at T0 and T1, blood samples will be collected in the morning after overnight fasting (two 6 mL yellow cap tubes for biochemical analyses); tubes will be then centrifuged at 3000 rpm for 15 min, aliquoted (each aliquot will have a volume of 500 microliters), and frozen (−20 °C or −80 °C) until shipment/analysis. Sera samples will be thawed just before the assay and will be analysed on an automated immunoassay system (Ella Simple Plex, Bio-Techne, Minneapolis, MN, USA) to measure serum levels of BDNF, NfL, and GFAP.

4.Time pattern of recovery during rehabilitation

The time pattern of recovery during treatment will be assessed by administering the following tests at the beginning (T0), at the end of the treatment (T1), and every 5 treatment sessions:Box and block test [66];10 m Walk Test [67].

During the execution of the motor tasks required by the two tests, only at T0 and at T1, where possible, patients will be instrumented with inertial sensors and surface electromyography to obtain quantitative information on their motor performance.

5.Follow-up

At the end of treatment, the patient will be contacted every month for the following 6 months, and the following questionnaires will be administered:Ad hoc questionnaire on the rehabilitation activity performed (type of rehabilitation setting, number of sessions, frequency, duration, type of treatment, etc.);Modified Barthel Index;EQ-5D-5L.

In case the patient is unable to reach the clinical centre, the questionnaires will be administered by phone or other remote connections. As a matter of fact, those scales can be administered remotely and allow the evaluation of general aspects related to skills and participation.

### 2.13. Costs, Sustainability, and Acceptability Assessments

The sustainability of the proposed solutions will be analysed through the comparison of their estimated costs and effects. We will employ the following analyses: cost-effectiveness analysis, cost–utility analysis, and budget impact analysis.

Cost-effectiveness analysis (CEA) will compare the costs and clinical outcomes of the alternative rehabilitation models being studied. The cost-effectiveness ratio (ICER) will be calculated as the difference in costs between the alternative rehabilitation models tested in the clinical study and the difference in clinical outcomes (objective measures by physical units). The ICER represents the additional cost incurred to achieve an incremental unit of effectiveness, that will be assessed considering primary and secondary outcomes. Cost–utility analysis (CUA) will assess and compare the efficiency of alternative rehabilitation interventions by measuring health outcomes in terms of utility, a measure of general well-being or quality of life (subjective measures), relative to the costs incurred to achieve these outcomes. Utilities will be evaluated using standardised measures based on quality of life. Each health condition identified through generic health-related quality of life questionnaires (EQ-5D-DL) will be associated with available utility scores specific to Italy [68]. The incremental cost–utility ratio (ICUR) will serve as the key metric, calculated as the ratio between differences in costs and differences in utility across the analysis groups.

From the perspective of the payer, the expected outcome of the budget impact analysis is the assessment of the financial impact (differences in direct health costs) over a 3–5-year period for the diffusion of a mix of robotic-based rehabilitations, compared to traditional rehabilitation. The financial impact will be assessed by considering the direct health costs associated with the different rehabilitation regimes, varying projections of robotic market uptake, and the degrees of substitutability between the compared rehabilitation regimes. Sensitivity analysis will be performed to assess the robustness and reliability of the results, evaluating how small variations in the variables considered affect the synthesis outcomes (ICER, ICUR, and budget impact).

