#### 2.13.1. Questionnaire for Patients

Several questionnaires will be provided to patients to analyse the following:
Acceptability and usability
a.Technology Acceptance Model [69]: after 5 sessions, after 15 sessions, at T1;b.Ad hoc questionnaire for needs and available solutions and perception of their relative complexity: at T0 and T1;Satisfaction (ad hoc questionnaire): at T0 and T1;Confidence and knowledge of ICT technologies (ad hoc questionnaire): at T0;Costs (ad hoc questionnaire): at T0, after 15 sessions, at T1;Quality of life (EQ-5D-5L [62]): at T0, after 15 sessions, at T1.

The ad hoc questionnaires for patients are provided in Supplementary Materials S1.

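### The key cost-utility ratio divides by a difference in utility rather than in QALYs, so duration is missing from its denominator

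*Protocol article*

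**What the plan says.** Section 2.13 of the protocol article describes the cost-utility analysis as "measuring health outcomes in terms of utility, a measure of general well-being or quality of life (subjective measures), relative to the costs incurred". Each EQ-5D health state "will be associated with available utility scores specific to Italy". The section then states: "The incremental cost–utility ratio (ICUR) will serve as the key metric", and gives its derivation as "calculated as the ratio between differences in costs and differences in utility across the analysis groups".

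The data schedule comes from three places:

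- Section 2.13.1: "Quality of life (EQ-5D-5L [62]): at T0, after 15 sessions, at T1".
- Section 2.12.2, item 5: after treatment "the patient will be contacted every month for the following 6 months", and the EQ-5D-5L is among the questionnaires given. Table 1 confirms T2.1 to T2.6. Together with the treatment period this makes nine EQ-5D-5L assessments.
- Section 2.13.1, on patient costs: "Costs (ad hoc questionnaire): at T0, after 15 sessions, at T1". Table 1 agrees, and no cost questionnaire is scheduled during follow-up.

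The article does not mention QALYs, an area under the utility curve or any other time weighting. The only horizon in section 2.13, three to five years, belongs to the budget impact analysis.

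**The concern.** Costs accumulate over time, whereas a utility score describes a state at one moment. A ratio of the first to a difference in the second has no time in its denominator, with three consequences:

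- A gain that lasts six months and one that disappears after T1 give the same ratio if T1 supplies the utility difference.
- With nine assessments and none nominated, the value of the key metric depends on which visit is used.
- The result is a cost per utility point. It cannot be set against a cost per QALY from another study or against a threshold expressed per QALY.

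Section 2.1.2 makes economic sustainability for patient, payer and society a stated objective, so the unit of the key metric matters to those readers. The problem lies in how the denominator is derived. It is separate from the instability of any ratio whose denominator is near zero, and it would remain if the effect were large.

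**Working it through.** The article states no ICUR, utility difference or QALY figure, so there is nothing to reproduce. The check is how far the written denominator can lie from a QALY difference on the trial's own visit schedule.

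**Inputs from the article.** Section 2.10 puts the end of treatment at 5 weeks for inpatients and 8.3 weeks for outpatients. Follow-up runs six months beyond T1, taken as 26 weeks.

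**Assumptions.** The arms do not differ in utility at T0. The difference rises linearly to D at T1 and then changes linearly to g × D at T2.6. With a linear rise, the assessment after 15 sessions does not alter the area.

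**Formula.** With w the weeks from T0 to T1:

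QALY difference = D × [w/2 + 26 × (1 + g)/2] / 52

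Factor = D / (QALY difference), which does not depend on D.

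| Trajectory after T1 | Inpatients (w = 5) | Outpatients (w = 8.3) |
|---|---|---|
| Sustained (g = 1) | (2.5 + 26)/52 = 0.548; factor 1.82 | (4.15 + 26)/52 = 0.580; factor 1.72 |
| Fades to zero (g = 0) | (2.5 + 13)/52 = 0.298; factor 3.35 | (4.15 + 13)/52 = 0.330; factor 3.03 |
| Doubles (g = 2) | (2.5 + 39)/52 = 0.798; factor 1.25 | (4.15 + 39)/52 = 0.830; factor 1.21 |

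A utility difference taken at T1 is therefore about 1.2 to 3.4 times the QALY difference in these cases.

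**Choice of visit.** If T2.6 supplies the difference, the sustained case is unchanged. In the fading case the denominator is zero and the ratio is undefined. In the doubling case the factor becomes 2/0.798 = 2.51 for inpatients and 2/0.830 = 2.41 for outpatients.

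**Choice of horizon.** Over T0 to T1 alone, the factor is 52/2.5 = 20.8 for inpatients and 52/4.15 = 12.5 for outpatients. The same linear rise to T1 yields 8.3/5 = 1.66 times the QALYs in outpatients, yet the written denominator is identical.

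**Direction.** The factor equals 1 when w/2 + 13 × (1 + g) = 52. For inpatients this gives g = 49.5/13 − 1 = 2.81, and for outpatients g = 47.85/13 − 1 = 2.68. Beyond that, the T1 difference is smaller than the QALY difference. Example for inpatients: a difference of 0.01 at T1 rising to 0.05 at T2.6 gives 0.01 × (5/52)/2 + 0.5 × (0.01 + 0.05)/2 = 0.0005 + 0.0150 = 0.0155 QALYs, which is 1.55 times the T1 difference.

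**The case against.** The strongest reply is that this is condensed wording in a journal article. Section 2.20 cites a study protocol that is not shown. QALY derivation, horizon and baseline adjustment are commonly left to such a document or to a health-economic plan. The sentence names no visit and does not say that utility is read at one time point, so it could be shorthand for utility accumulated over follow-up. Section 2.1.2 also announces a cost-effectiveness and cost-utility model, in which duration could enter.

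Much of this stands. A reader should not infer that the investigators will in fact report a cost per utility point, or that no fuller plan uses QALYs; the article cannot show either. What remains is that the article does more than stay silent. It writes out the ratio for its key metric and describes the denominator as a quality-of-life measure scored from EQ-5D states. The announced model has no stated effect unit or horizon. The sensitivity analysis in section 2.13 covers small variations in the inputs. Neither changes the unit of the stated denominator.

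A reader might also infer that the written ratio always makes RADTs look more cost-effective than they are. The documents do not support that. The discrepancy reverses if the effect grows enough after T1. Its meaning also reverses if RADTs prove cheaper and slightly worse, because too large a denominator then understates the saving per QALY lost.

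**Conclusion.** The point holds as a defect in the stated definition. Applied as written, the ICUR is a cost per utility point that ignores duration and depends on an unstated choice of visit. Its distance from a cost per QALY has no single value, because it depends on the visit, the horizon and the trajectory of the utility difference. The range of about 1.2 to 3.4 rests on a T1-based denominator, a horizon to T2.6 and three assumed trajectories. A shorter horizon gives much larger factors, and a late-growing effect gives factors below 1.

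Only the secondary economic objective is affected. The non-inferiority analysis of the modified Barthel Index and the sample size are untouched. The change is worth making before the economic analysis begins; if a fuller document already specifies QALYs, it reduces to aligning the published wording.

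**What to change.** In section 2.13, define the ICUR denominator as the difference in QALYs between groups. Compute QALYs per patient as the area under the EQ-5D-5L utility curve over a stated horizon, and adjust the group difference for T0 utility. Use actual assessment dates as the time axis: at the planned frequencies the assessment after 15 sessions falls at week 3 (15/5) for inpatients and week 5 (15/3) for outpatients, and T1 at 5 and 8.3 weeks.

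Count costs over the same horizon. The patient cost questionnaire ends at T1 while the EQ-5D-5L continues to T2.6, so there are two workable choices:

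- Use T0 to T1 for the full-cost analysis (patient and society), and say that it captures nothing after treatment.
- Extend to T2.6 for those costs that can be derived from the monthly questionnaire on rehabilitation activity, and state that limit.

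The cost is modest. The EQ-5D-5L assessments are already scheduled, so neither choice needs a new visit. It takes some extra derivation work and a rule for missing monthly EQ-5D-5L values, and the reported ratio may look less favourable than a cost per utility point.
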